### Randomization

In this trial, eligible patients who consent to participate will be randomly assigned to one of four groups via a central randomization system for clinical research in a ratio of 1:1:1:1 by an independent researcher, who will not be involved in the implementation or statistical analysis of the trial. Random number lists will be created by PROCPLAN of SAS 9.2 (SAS Institute Inc., Cary, NC, USA). The randomization allocation will use sequentially numbered, opaque, and sealed envelopes. The participants’ screening sequence numbers will be printed outside the envelope, whereas the group names will be printed inside. After a participant has met all selection criteria, signed the informed consent form, and completed the baseline assessments, the researcher will inform the statisticians in the center. The statisticians will open the envelope according to the participant’s screening sequence number and then assign the participant to one of the four groups.

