### Blinding

Due to the operation characteristics of acupuncture, acupuncturists will be asked to apply the different methods of stimulation, they will not be blinded to treatment allocation for the different locations in each group. However, participants will be blinded to group assignment, and they will be informed that there are four methods of acupuncture treatment provided in this study and will accept one of them in a separate compartment. Each participant will be treated separately to prevent any exchange of study information. In addition, the outcome assessors, data recorders, acupuncturists, and statisticians will all operate independently; the randomization staff and acupuncturist will know the allocation information, while the outcome assessor and statisticians will stay blind to this information throughout the study. Unblinding will not be done until the completion of data analysis, and after the data analysis, we will have a blinded interpretation of the study results to minimize misleading data interpretation. In short, we will implement the three separation principles of researchers, operators, and statisticians for the sake of reducing the risk of bias.

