### Data collecting and monitoring

The governance of this study will be carried out by the trial steering committee (TSC), composed of the primary investigators and statisticians, who will oversee the entire study conduct to ensure that all researchers participating in this study are following the proposed protocol. A monthly meeting will be conducted where the TSC can supervise the progress and the data quality of this study and share suggestions if problems occur. The Ethics Committee will hold an annual meeting to monitor the implementation of the entire trial.

In this study, the data that includes observation time points, scanning time points, outcome measures, adverse events, and safety evaluations will be collected at baseline and weeks 4, 8, and 12 after the intervention using the case report form. And a special assistant will be responsible for reviewing data integrity, accuracy, and consistency. Patients will be assigned to a quiet room for psychological factor assessments. In order to ensure the consistency of source data, all the scales will be assessed by the same researcher during the study. Meanwhile, the research data will be input into EpiData electronic database. For ensuring the accuracy of data entry, data will be entered independently by two researchers, and then the discordances will be resolved by tracing source data.

When the trial is completed, the database will be locked by the data management team, after which the researchers can no longer modify the data. Both paper files and electronic documents will be preserved for at least 5 years after publication. If readers and reviewers have any questions, they can contact the corresponding author for access to the original data. Patient information will remain anonymous, including name, ID number, and telephone number.

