### Statistical analysis

Before the data analyses, the research group will provide a statistical scheme to the statisticians. The scheme will include the required data and processing method. The data will be processed and analyzed by the statisticians by the scheme.

Intention-to-treat statistical analysis will be conducted. Missing data will be treated by imputation methods depending on the type: missing completely at random, missing at random, or not at random. Per-protocol analysis will include only patients who attended at least 80% of the sessions and completed the follow-up in the allocated intervention group.

Statistical analyses will be performed with SPSS 22.0 statistics software (IBM Corporation, Armonk, NY, USA). The data analysis process will be completed by statisticians who are independent of the research team and blinded to the test settings. A *t*-test and Wilcoxon test will be used to compare the numerical variables in the within-group analyses, including the WOMAC, VAS, AIMS2-SF, BAI, and BDI. Analysis of variance and the Kruskal-Wallis test will be used for numerical variables in the between-group analyses, including age, height, weight, scores of VAS, WOMAC, AIMS2-SF, BAI, BDI, and Credibility/Expectancy Questionnaire. The chi-squared test and one-way analysis of variance (ANOVA) will be used for categorical variables such as the demographic and baseline characteristics. The available data of the four groups (group A, group B, group C, and group D) will be tested by bilateral tests and the confidence intervals are all 95% bilateral, with a *P* value less than 0.05 being statistically significant.

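### The Randomization section has statisticians open the envelopes and assign patients, although it also gives that task to an independent researcher and three other sections call statisticians blind

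*Protocol article*

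**What the plan says.** All places are in the protocol article.

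- **Randomization, opening sentence.** Patients are assigned "via a central randomization system for clinical research", and this is done "by an independent researcher, who will not be involved in the implementation or statistical analysis of the trial".
- **Randomization, later in the same paragraph.** Sealed opaque envelopes are used; "screening sequence numbers will be printed outside the envelope" and the group name is inside. Once eligibility, consent and baseline are complete, "the researcher will inform the statisticians in the center. The statisticians will open the envelope according to the" screening number, "and then assign the participant to one of the four groups". The statisticians are the subject of both verbs, opening and assigning.
- **Blinding.** Randomization staff and the acupuncturist know the allocation, whereas "the outcome assessor and statisticians will stay blind to this information throughout the study". Unblinding is placed after the data analysis.
- **Statistical analysis.** The analysis is done by "statisticians who are independent of the research team and blinded to the test settings".
- **Discussion, Strict quality control.** Statisticians are again listed among those who are not to know the grouping.
- **Study setting and recruitment.** Each patient receives a unique randomization number at enrolment. The Randomization section does not use it.

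**The concern.** Two parties are named for one task. One of them carries the job title that the rest of the article describes as blind. Whoever opens an envelope reads the group name, so a statistician who does this for each patient holds the allocation list.

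The acupuncturists cannot be blinded, and the primary outcome, the WOMAC, is reported by the patient. Blinded analysis is therefore one of the few protections that the trial can fully control, and the article presents it as a safeguard. Decisions remain at that stage: the Statistical analysis section names both analysis of variance and the Kruskal-Wallis test, makes imputation depend on the type of missingness, and needs per-protocol membership to be settled. If the people making these decisions know the allocation, the final report could not truthfully claim a blinded analysis.

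**Working it through.** No formula applies. The point depends on no error rate, effect size or sample size, so the check is a comparison of the statements.

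**Step 1. Who assigns?**

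| Place | Party who assigns | Role in the analysis |
|---|---|---|
| Randomization, opening sentence | An independent researcher | None, by explicit statement |
| Randomization, envelope procedure | The statisticians in the center | Not stated |

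The two rows name different parties. The envelope procedure also has a researcher who notifies the statisticians, without saying whether this is the independent researcher. If it is, that person reports a patient as ready and does not assign.

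**Step 2. Who learns the allocation?**

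| Place | Do statisticians know the allocation? |
|---|---|
| Randomization, envelope procedure | Yes: they open the envelope that holds the group name |
| Blinding | No, throughout the study |
| Statistical analysis | No |
| Discussion, Strict quality control | No |

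The first row conflicts with the other three if the word means the same people throughout.

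**Step 3. Could the word mean different people?** The conflict in Step 2 would disappear if the statisticians in the center were a separate randomization team. No section says so. The Blinding section points the other way: it treats randomization staff and statisticians as two parties with opposite access to the allocation. Even if the label is loose, Step 1 still leaves two parties assigning.

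**Step 4. Extent.** Four groups of 50 give 4 × 50 = 200 allocations. On the literal reading statisticians see all 200. If the center's statisticians are separate staff who take no part in the analysis, the analysts see none. The article does not settle which holds.

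**The case against.** The strongest reply is that the statisticians in the center are simply the randomization staff of the Blinding section under a loose name, and that the analysts are other people, as the independence claimed in the Statistical analysis section suggests. This is plausible, and it is why the text cannot be taken as proof that the analysts will be unblinded. It does not remove the point, because the separation is nowhere stated.

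It is also fair to say that the likely harm is limited. The research group gives the statisticians a scheme with the processing method before analysis, which narrows their discretion, and an analyst cannot alter a self-completed WOMAC. Envelopes are opened only after baseline, so no breach of allocation concealment is shown.

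A reader might infer more, in four ways that the article does not support:

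- **That the protection against bias does not exist.** This holds only on the literal reading.
- **That a central system and sealed envelopes are incompatible.** A list generated centrally and delivered in envelopes held at the center is a workable chain. The conflict is over who opens and assigns.
- **That statisticians on the steering committee, which is "composed of the primary investigators and statisticians", break the blind.** The committee is said to supervise progress and data quality. Review of outcomes by arm is not mentioned.
- **That envelopes keyed to screening numbers will unbalance the arms.** The article gives neither a block size nor a screen-failure rate, so any size for this would rest on assumptions. Unequal arm sizes arising this way would not bias the comparison and would cost little: a 45 to 55 split keeps 4 × 0.45 × 0.55 = 0.99 of the efficiency of an equal split.

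**Conclusion.** The contradiction stands and should be fixed. The Randomization section names two parties as assigning patients, and one of them is a role that three other places call blind. Followed as written, the blinded analysis would not hold. Followed as perhaps intended, it would, but the article does not state that intention.

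The exposure is therefore all 200 allocations on the literal reading, and none for the analysts if a separate team exists. No numerical effect on bias, power or type I error can be derived, and none is claimed. The conclusion rests on one reading, that the word statisticians has the same meaning throughout, and nothing in the article contradicts that reading.

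**What to change.** 1. In the Randomization section, replace the statisticians with the independent researcher already named, as the only party who opens envelopes or releases allocations. State that this person takes no part in the analysis.
2. Key each allocation to the randomization number described under Study setting and recruitment, not to the screening number, and say in one sentence how the central system and the envelopes fit together.
3. Give the analysts a database with masked arm codes.
4. Align the Blinding and Statistical analysis sections and the quality-control part of the Discussion, using one term for randomization staff and another for analysts.
5. Trial status says that recruitment had not begun and gives a planned start of September 1, 2021, but the article was published on August 20, 2022, so enrolment may be under way. If it is, record who has opened envelopes and give the analysis to someone who has not.

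The cost is wording and a small change of procedure. The independent researcher, the central system and the randomization number are already in the plan. Item 5 needs another analyst only if those who opened envelopes were also due to do the analysis.

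### The Randomization section has statisticians open the allocation envelopes and assign the arm, which contradicts its own first sentence and the stated blinding of the statisticians, so blinding of the analysis is not assured

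*Protocol article*

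**What the plan says.** The Randomization section describes the assigner twice. Its first sentence says that patients are assigned through a central system "by an independent researcher, who will not be involved in the implementation or statistical analysis of the trial". Its closing sentences describe sealed envelopes: the outside carries the screening number and "the group names will be printed inside". Once eligibility, consent and baseline assessment are complete, "the researcher will inform the statisticians in the center". Then: "The statisticians will open the envelope according to the" participant's screening number, "and then assign the participant to one of the four groups".

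The Blinding section divides the staff in two. Randomization staff and the acupuncturist know the allocation, while "the outcome assessor and statisticians will stay blind to this information throughout the study". It adds that unblinding waits until the data analysis is complete, and that a blinded interpretation of the results follows.

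The Statistical analysis section assigns the analysis to "statisticians who are independent of the research team and blinded to the test settings". The Strict quality control section of the Discussion again lists statisticians among those who will not know the patients' grouping.

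**The concern.** The role that opens each envelope and the role declared blind carry the same name. A person who opens an envelope with an uncoded group name inside knows that patient's arm from that moment. If that person also analyses the data, the analysis is not blind.

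The protocol relies on this safeguard. Blinding presents the separation of researchers, operators and statisticians as a protection against bias, and Strict quality control repeats it. The acupuncturists cannot be blinded, so the remaining blinding (participants, assessors, statisticians) carries the claim. A reader of the eventual report who is told that the statisticians were blind could not reconcile that with the procedure by which patients were allocated.

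**Working it through.** No arithmetic bears on who knows the allocation. The check sets the sections side by side.

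| Section | Who assigns or opens envelopes | Do statisticians know the arm? |
|---|---|---|
| Randomization, first sentence | Independent researcher, outside the implementation and the statistical analysis | Not implied |
| Randomization, last sentences | Statisticians in the center | Yes, from the group name in the envelope |
| Blinding | Randomization staff (named as knowing the allocation) | No, throughout the study |
| Statistical analysis | Not addressed | No |
| Strict quality control | Not addressed | No |

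**Step 1. Conflict inside Randomization.** The first sentence and the last name different assigners. The first assigner has no part in the statistical analysis. The last is a group named for statistics. Nothing says that the two are the same people.

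**Step 2. Conflict across sections.** Blinding puts randomization staff and statisticians in one sentence as opposite categories: the first know the allocation, the second do not. Randomization gives the first category's task to the second category by name.

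**Step 3. Possible readings.** Three are open, and each can be followed to its consequence.

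- *The envelope openers are the analysts.* They know the arm of all 4 × 50 = 200 patients before the analysis, and the blinding claims in the other three sections are false.
- *The envelope openers are separate statistical staff at the center.* The analysts may know 0 of 200 allocations. But Blinding's unqualified statement about statisticians is then wrong as worded, and the first sentence of Randomization still names someone else as assigner.
- *The envelope openers are the independent researcher or randomization staff under a loose label.* The analysts may again know 0 of 200, and the defect is the label alone.

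**Step 4. Result.** The number of allocations known to the analysts runs from 0 to 200 depending on the reading, and the document does not choose between readings. The wording needs correction under all three.

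**The case against.** The strongest reply is that the clash is one of labels. Randomization speaks of statisticians in the center, in a section that opens with a central system and an assigner who takes no part in the analysis. Blinding recognises randomization staff as a distinct role. Read together, the envelope openers may well be those staff. This stands to the extent that the identity of allocators and analysts rests on one undifferentiated word. It does not remove the contradiction, because no section states the separation. Nor is this detail that a fuller protocol or an SAP would be expected to supply: the point rests on statements in the article that conflict with each other.

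Other safeguards also stand. Envelopes are opened only after eligibility, consent and baseline assessment. Outcome assessors are to be blind. The WOMAC is self-administered. Data are entered twice and the database is locked. These limit the consequences, although none of them blinds the analysis.

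Four stronger inferences are tempting, and the documents do not support them:

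- *That the analysts certainly know every arm, so blinded analysis does not exist.* This treats the first reading above as established.
- *That unblinded statisticians would choose the imputation method, choose between ANOVA and Kruskal-Wallis, and decide per-protocol membership.* Statistical analysis says that the research group supplies a scheme, including the processing method, before the analysis, and that the statisticians work to it. Per-protocol membership follows a stated rule: attendance at 80% or more of sessions, and completed follow-up in the allocated group.
- *That the steering committee leaks allocation.* Data collecting and monitoring describes it as "composed of the primary investigators and statisticians", meeting monthly, but does not say that it sees allocation or results by arm, nor that its statisticians perform the analysis.
- *That a central system and sealed envelopes are incompatible.* A centrally generated list carried out through envelopes held at the center is a coherent procedure.

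**Conclusion.** The Randomization section is wrong as written. It contradicts itself on who assigns patients, and it contradicts Blinding, Statistical analysis and Strict quality control on whether statisticians know the allocation. The supportable conclusion is that blinding of the analysis is not assured, which is weaker than saying that it is absent.

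The conclusion rests on two features of the text: the same word is used for both roles without distinction, and no coding of the group name inside the envelope is described. If the authors intended separate people, stating so would resolve the conflict in substance.

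The exposure covers anywhere from none to all of the 200 allocations, and with it the blinding of the primary and secondary analyses. The size of any resulting bias cannot be computed from the document. Severity is moderate: a stated protection is undermined by the protocol's own procedure, the correction is simple, and the other safeguards do not depend on it.

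**What to change.** In Randomization, replace the closing sentences so that the independent researcher already named there, identified as the randomization staff of the Blinding section, holds and opens the envelopes and passes the arm only to the treating acupuncturist. Remove the statisticians from the allocation step.

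In Blinding or Statistical analysis, add that the analysing statisticians have no access to the envelopes or the allocation list, and that they receive only masked group codes until the analysis and its blinded interpretation are finished. Codes are needed because the planned between-group tests cannot be run on data pooled over arms. They are sufficient because ANOVA and Kruskal-Wallis give the same result whichever label each group carries.

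Strict quality control then needs no change on this point. The cost is a few sentences and one reassigned task, given to staff the plan already has. Sample size, outcomes and treatment are unaffected. If allocation has already taken place, the sponsor should instead record who opened the envelopes and whether those people took part in the analysis, and report the blinding of the analysis accordingly.

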### Blinding

Due to the operation characteristics of acupuncture, acupuncturists will be asked to apply the different methods of stimulation, they will not be blinded to treatment allocation for the different locations in each group. However, participants will be blinded to group assignment, and they will be informed that there are four methods of acupuncture treatment provided in this study and will accept one of them in a separate compartment. Each participant will be treated separately to prevent any exchange of study information. In addition, the outcome assessors, data recorders, acupuncturists, and statisticians will all operate independently; the randomization staff and acupuncturist will know the allocation information, while the outcome assessor and statisticians will stay blind to this information throughout the study. Unblinding will not be done until the completion of data analysis, and after the data analysis, we will have a blinded interpretation of the study results to minimize misleading data interpretation. In short, we will implement the three separation principles of researchers, operators, and statisticians for the sake of reducing the risk of bias.

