#### Group B

In group B, subjects will be treated with EA for 4 weeks. The acupoints and acupuncture operation are the same as the MA group, but after *deqi*, an electrical apparatus (HANS-200A acupoint nerve stimulator, Nanjing Jisheng Medical Co, Ltd) will be connected. When both alligator clips are connected to paired needles, it produces electric currents to stimulate acupoints. The electric wave mode will be the dense-sparse wave; sparse wave and dense wave appear alternately, each wave lasting for 1.5 s to avoid body adaptation caused by the continuous output of a single waveform. The power of the electric current will be adjusted to make each acupoint feel the electric stimulation but still comfortable during the treatment process. The needle will be retained for 30 min in each session. EA treatment will be applied once a day, 5 sessions per week for 4 consecutive weeks, and rest for 2 days between treatments.

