#### Group C

In group C, subjects will be treated with WA for 4 weeks. The acupoints, location, and acupuncture operation will be the same as those described for the MA group. After *deqi*, acupuncturists will insert a piece of moxa pillar (3 cm) into the end of the needle, and light the tip of the moxa pillar, when the moxa pillar burning is completed, the acupuncturist will remove the ashes. When the time reaches 30 min, the acupuncturist will remove the acupuncture needles and check thoroughly for any possible blisters or bleeding. WA treatment will be applied once a day, 5 sessions per week for 4 consecutive weeks, and rest for 2 days between treatments.

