#### Group D

In group D, the non-acupoints used in the SA are all located 1cm away from the outer side of the midline of the lower extremity of the six acupuncture points selected in the MA group. Patients in the SA group will undergo the same procedures as those in the MA group. The needle depth is 1~2mm, and the needle will be directly retained for 30 min without any manipulation in the whole procedure to avoid the *deqi* sensation as much as possible. The SA treatment will be applied once a day, 5 sessions per week for 4 consecutive weeks, and rest for 2 days between treatments.

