#### Secondary outcome

① We will use the Western Ontario and McMaster Universities Osteoarthritis Index (WOMAC) evaluation at weeks 8 and 12 as the secondary outcome measure.② The pain visual analog scale (VAS) [24]: The VAS is an internationally recognized 10-point scale selected to quantitatively evaluate the level of knee pain during the study. It scores from “0 (none),” “about 2 (mild),” “around 5 (moderate),” “almost 8 (severe),” and “nearly 10 (unbearable)” spaced along the continuum. During the experiment, the VAS assessments will be performed at baseline and weeks 4, 8, and 12 respectively by independent assessors who are not involved in acupuncture treatments (asking subjects to indicate the pain intensity at the most painful points during walking and ascending/descending a step and overall).③ Arthritis Quality of Life Measurement Scale Simplified Scale (AIMS2-SF) [25]: We will use the Chinese version of the Arthritis Quality of Life Measurement Scale Simplified Scale by the Fudan University School of Public Health to assess the quality of life. Because this experiment is aimed at KOA patients, 5 items involving hands and arms in the physical dimension of this scale will be removed, and only the remaining 21 items will be used. All items are scored on a scale of 1 to 5, with the total score represented by the sum of 5 dimensions. The higher the score, the better the quality of life. The evaluation will be performed at baseline at weeks 4, 8, and 12 respectively after randomization.④Credibility/Expectancy Questionnaire: The Credibility/Expectancy Questionnaire is a quick and easy-to-administer scale for measuring treatment expectancy and rationale credibility for use in clinical outcome studies [26]. Participants will be asked “How much do you feel acupuncture therapy will help to reduce your symptoms?” at baseline.⑤ Emotional monitoring: Mood changes, such as depression and anxiety, are common concomitant symptoms of KOA. In order to monitor the impact of emotional changes on the condition of KOA, we will use the Beck Anxiety Inventory (BAI) [27] and Beck Depression Inventory (BDI) [28] to evaluate the emotional state of patients in this trial. The evaluation will be performed at baseline and weeks 4, 8, and 12 respectively after randomization.

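### Participants are said to be blinded to group, but electro- and warm-acupuncture participants can recognise their method, and a pre-treatment credibility question cannot show whether credibility differed by arm

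*Protocol article*

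**What the plan says.** The Blinding section of the protocol article states, for all arms, that "participants will be blinded to group assignment, and they will be informed that there are four methods of acupuncture treatment provided in this study". Two safeguards bear on participants. Each is treated alone (Blinding), and needless talk with the acupuncturist is ruled out (Strict quality control).

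The intervention sections describe what participants experience:

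- **EA (Group B):** the current is to be "adjusted to make each acupoint feel the electric stimulation but still comfortable during the treatment process".
- **WA (Group C):** the acupuncturist is to "insert a piece of moxa pillar (3 cm) into the end of the needle, and light the tip of the moxa pillar". The moxa then burns out and the ash is cleared away.
- **SA (Group D):** "The needle depth is 1~2mm, and the needle will be directly retained for 30 min without any manipulation". Apart from depth, manipulation and needle sites, the sham follows the MA procedure.

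The primary outcome is the WOMAC total at week 4, which patients complete themselves with help from doctors (Primary outcome).

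The only measure of credibility or expectation is the Credibility/Expectancy Questionnaire. Participants are asked how far they feel that "acupuncture therapy will help to reduce your symptoms". Secondary outcome places it at baseline, and Table 1 marks it at week 0 only. The Abstract lists it among the secondary outcomes, and Statistical analysis compares it between groups in a list that ends "BAI, BDI, and Credibility/Expectancy Questionnaire".

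**The concern.** The blinding claim has no qualification, yet two of the four arms are delivered with a cue that the participant is meant to feel or cannot miss. Neither cue has a dummy counterpart elsewhere. With a self-reported primary outcome the participant is in effect the assessor, so blinding the outcome assessor does not protect against a participant's own expectation.

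At stake is how EA versus SA and WA versus SA are read. If having current or moxa changes what a patient expects, the difference from sham contains that change as well as any effect of the treatment itself. A credibility questionnaire is the usual way to look for this. Here it is taken at a time, and worded in a way, that cannot reveal it.

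**Working it through.** No stated figure bears on this point, so the check sets the sections side by side.

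**Step 1. What each arm's participant can perceive** (Groups A to D)

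| Arm | Needling | Added cue | Inactive version of the cue in MA or SA |
|---|---|---|---|
| MA | 21~26 mm, manipulated to obtain and keep deqi | none | not applicable |
| EA | as MA | current set to be felt | none described |
| WA | as MA | moxa lit and burned on the needle | none described |
| SA | 1~2 mm, at non-acupoints, no manipulation, deqi avoided | none | not applicable |

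A participant who has been told that there are four methods, and who feels current or has moxa burned on the needle, can tell which method is being given. Separate treatment and limits on conversation stop information passing between people. They do not hide what the participant sees and feels. At 50 per arm this concerns 2 × 50 = 100 of 200 participants.

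**Step 2. Which comparisons with sham are affected**

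- EA versus SA: cue in EA, no counterpart in SA.
- WA versus SA: cue in WA, no counterpart in SA.
- MA versus SA: no current or moxa in either arm. Depth, manipulation and deqi still differ, so masking is attempted but not assured.

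That is two of three. For each of those two, the difference in mean WOMAC can be written as

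observed difference = difference due to the treatment itself + difference due to expectation.

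The trial observes only the sum.

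**Step 3. Whether the questionnaire can separate the two terms**

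- *Timing.* The Randomization section has baseline assessments finished before the envelope is opened. Table 1 is less clear: it marks randomization at −1 week, and both allocation and the questionnaire at week 0. Under either reading the questionnaire precedes treatment, which Table 1 starts in week 1.
- *Content.* The question concerns acupuncture in general, not the method assigned.
- *Consequence.* If the Randomization section is followed, the score X is fixed before allocation, so E(X | EA) − E(X | SA) = 0 by randomization. The same holds for WA versus SA. The planned between-group test at 0.05 then rejects about 5% of the time, however far credibility of the assigned treatments later diverges. If the week 0 questionnaire instead followed allocation, it would still come before the participant had experienced any treatment.

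No later credibility question and no guess of allocation appears in Table 1 or under the outcomes. Analysis cannot recover what is not collected.

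**The case against.** Four points can be made for the plan.

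1. **Blinding may mean only that participants do not know which method is the sham.** A reader might infer from the cues that EA and WA participants are simply unblinded. The documents do not support that. Participants are told of four acupuncture methods, and the article does not say whether they are told that one is a sham. Recognising the method is not the same as knowing active from sham, and an SA participant may take the needling as genuine. This stands and limits the point. The text nevertheless says group assignment, which is broader than the active-or-sham distinction.

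2. **The stated aim is to compare MA, EA and WA.** Giving each as practised is a legitimate design, and recognition is then part of the method. This also stands. A reader might extend the concern to every pair that includes EA or WA, but comparisons between active arms raise no question about sham credibility, and in EA versus WA both arms carry a cue.

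3. **The between-group test of the questionnaire may be only a baseline check.** Statistical analysis lists it with age, height and weight. That is a fair reading of that section, but the Abstract and Secondary outcome class it as an outcome, and a baseline check still says nothing about credibility during treatment.

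4. **Measuring credibility does not remove bias.** True. It shows whether there is a difference to worry about.

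**Conclusion.** The point holds in a limited form and should be corrected. As described, EA and WA participants can recognise their method, so blinding to group assignment is not achieved for them. EA versus SA and WA versus SA can therefore include expectation, and the questionnaire as scheduled cannot show whether credibility differed by arm.

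The size of any bias cannot be derived. The article gives success rates but no standard deviation for WOMAC and no estimate of an expectation effect, so expressing the bias as a share of the detectable difference would be guesswork. That expectation does differ by arm is a possibility the design leaves open, not something the documents show.

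A reader might also conclude that MA versus SA, having no current or moxa, is securely masked. The intervention sections do not support this, given the differences set out in Step 1.

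The conclusion assumes that no dummy stimulator or mock moxa is used beyond what the article describes.

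**What to change.** **(a) Blinding and interpretation.** Restate the Blinding section to say that:

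- outcome assessors and analysing statisticians are to be blinded (the Randomization section has statisticians open the envelopes, so the text should make clear which are meant);
- EA and WA participants can recognise their modality;
- masking of MA versus SA is attempted but not assured.

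Describe EA versus SA and WA versus SA as total effects that may include expectation.

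**(b) Questionnaire.** Repeat the Credibility/Expectancy Questionnaire after an early treatment session, asked about the assigned treatment, and report it by arm. Treat the baseline score as a baseline variable or covariate, not a secondary outcome. Data collecting and monitoring has one researcher assess all scales, so the repeated form should be self-completed and kept from that person, or it will disclose the arm.

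A question asking for a guess of true or sham is optional and mainly informative for MA versus SA.

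**Cost.** A weaker blinding claim and one short extra questionnaire. The scale visits are at weeks 0, 4, 8 and 12, so this adds a data point, but participants already attend for treatment. No treatment changes. Trial status says that recruitment has not begun but gives a start of September 1, 2021. If it is under way, (a) applies in full, and the repeated questionnaire only to participants still to be treated.
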